**Methods:**

This is an 18-month cluster-randomized, open-label, parallel-arm controlled trial conducted at 14 public hospitals in the Perak state of Malaysia. Patients aged 60 and above, who have at least one medication and one comorbidity are eligible. A stratified-cluster randomization design is employed, with 7 hospitals assigned to the control arm and 7 hospitals assigned to the intervention arm. The MALPIP screening tool will be used in the intervention group to review the medications. If PIM is detected, the pharmacists will discuss with doctors and decide whether to stop or reduce the dose. The primary outcomes of this trial are the total number of medications and number of PIM. The secondary outcomes include fall, emergency department visits, readmissions, quality of life and mortality. Outcomes will be measured during enrolment, discharge, 6, 12, and 18 months.

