### Trial setting

The trial will be conducted in the state of Perak, which has one of the highest proportion (8.9%) of older adults aged 65 years and above in Malaysia [23]. The state is served by 14 public hospitals spread across the 10 administrative districts. In this study, seven hospitals will be randomized to intervention with the remaining seven hospitals serving as the control group (Fig. 1). In order to ensure a representative population is recruited, both general medicine wards or geriatric wards will be selected from each hospital, from both female and male wards.

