### Randomization

A stratified-cluster randomization design will be adopted for this trial, with the 14 hospitals serving as the unit of randomization. This design was chosen specifically to address the potential "contamination" effect that may arise among individuals within the same ward. The cluster design effectively controls for the potential "contamination" effect that may arise among individuals (pharmacists, doctors, patients) within the same ward, where changes in one individual's behaviour may have the potential to influence others. Furthermore, this approach offers the advantage of significant time savings compared to individual randomization. The principal investigator performed the randomization.

Given that larger and smaller hospitals may have different administrative capacities, it was crucial to ensure a balanced distribution of patients across both intervention and control arms. To achieve this, trial sites were stratified and clustered based on the number of yearly admissions in each hospital as follows:i.Hospitals with 4001–5000 yearly admissions (total of 5 hospitals; intervention: 3; control: 2)ii.Hospitals with 3001–4000 yearly admissions (total of 6 hospitals; intervention: 3; control: 3)iii.Hospitals with 1500–3000 yearly admissions (total of 3 hospitals; intervention: 1; control: 2).

This approach ensures a balanced and comparable distribution of patients in both the intervention and control groups.

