### Data analysis

All analyses will adhere to the intention-to-treat principle, complemented by per-protocol analysis as sensitivity analyses. Descriptive statistics will be employed to analyse the baseline characteristics of the patients. The change in the mean number of chronic medications and potentially inappropriate medications (PIM) across four time-points will be assessed using repeated measures ANOVA. Independent t-tests will be utilized to compare the number of emergency department (ED) visits and hospitalizations between the control and intervention groups. A p-value of less than 0.05 will be deemed statistically significant. IBM SPSS Statistics for Windows version 24 (IBM Corporation, NY, USA) will be employed for statistical analyses.

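### Hospitals are randomised, but the repeated measures ANOVA and t-tests treat patients as independent, so the nominal 5% error rate can be exceeded

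*Protocol article*

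**What the plan says.** The Randomization section sets up a stratified cluster design "with the 14 hospitals serving as the unit of randomization", and Trial setting gives the split: "seven hospitals will be randomized to intervention with the remaining seven hospitals serving as the control group". The hospitals fall into three strata by yearly admissions, allocated 3:2, 3:3 and 1:2 (intervention to control).

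The Data analysis section then names the tests. For both primary outcomes, the change in mean number "across four time-points will be assessed using repeated measures ANOVA". For service use: "Independent t-tests will be utilized to compare the number of emergency department (ED) visits and hospitalizations between the control and intervention groups". The significance threshold is 0.05. The section mentions no hospital effect, mixed model, generalised estimating equation, cluster-robust variance, cluster-level summary or stratum term.

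The Sample size calculation section works the same way: 189 patients per arm for a difference of 0.13 with SD 0.39, with no ICC or design effect.

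**The concern.** Patients in one hospital share pharmacists, doctors and prescribing habits, so their outcomes tend to be alike. The protocol article gives this as its reason for randomising hospitals: behaviour in a ward may spread from one person to another. When whole hospitals are allocated, differences between hospitals become part of the error of the treatment comparison, and there are only 14 hospitals to average over.

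A standard two-group repeated measures ANOVA or independent t-test takes its error from patients alone. Its standard errors are then too small whenever hospitals differ. An ordinary prescribing difference between two sets of seven hospitals could be reported as an effect of deprescribing on the primary outcomes, ED visits or readmissions. The article expects the results to feed into national deprescribing guidelines.

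**Working it through.** **Inputs from the protocol article.** 14 hospitals, 7 per arm; two-sided alpha 0.05; power 90%; difference 0.13; SD 0.39; 189 per arm (378 in total); 25% dropout; 500 enrolled. Mean cluster size is 378/14 = 27 after dropout, or 500/14 = 35.7 (about 36) as enrolled.

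**Assumed, because not given.** ICC 0.01 to 0.05; within-patient correlation 0.5; hospital-by-time variance 0, 1% or 2% of the total; equal cluster sizes.

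**1. The plan's own figure.** n per arm = 2 × (1.960 + 1.282)² × (0.39/0.13)² = 2 × 10.51 × 9 = 189.1, which agrees with the stated 189. Dropout: 378/0.75 = 504, against 500 stated. The sample size therefore counts 378 independent patients.

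**2. Patient-level test at one time-point (the t-tests).** The true variance exceeds the assumed variance by the design effect DE = 1 + (m − 1) × ICC. The actual two-sided error rate is 2 × [1 − Φ(1.96/√DE)].

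| ICC | DE, m = 27 | error | DE, m = 35.7 | error |
|---|---|---|---|---|
| 0.01 | 1.26 | 8.1% | 1.35 | 9.1% |
| 0.02 | 1.52 | 11.2% | 1.69 | 13.2% |
| 0.05 | 2.30 | 19.6% | 2.74 | 23.6% |

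Simulation (20,000 runs, 7 vs 7 hospitals) gave 8.3%, 11.1% and 19.7% at 27 per hospital, and 9.5%, 13.6% and 24.0% at 36. A t-test on the 14 hospital means stayed at 4.8% to 5.3%.

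**3. ANOVA between-group test.** This test uses each patient's mean over visits. Averaging shrinks patient noise but not a constant hospital effect, so the effective ICC rises. With four visits and ICC 0.05, the variance of a patient mean is 0.05 + 0.475 + 0.475/4 = 0.644, and the effective ICC is 0.05/0.644 = 0.078. At m = 36, DE = 1 + 35 × 0.0777 = 3.72 and the error rate is about 31% (simulated 32%). At m = 27, DE = 3.02 and the error rate is about 26%.

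**4. ANOVA group-by-time test.** A hospital effect that is constant over time cancels: the simulated error rate was 4.7% at ICC 0.05. A hospital-by-time component c does not cancel. It inflates the F statistic by about 1 + (m − 1)c/(e + c), where e is the within-patient residual variance. With four visits (3 numerator df, chi-square critical value 7.815) and total variance 1:

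- m = 27, constant hospital variance 0.02, c = 0.01: e = 0.5 × 0.97 = 0.485; factor 1 + 26 × 0.01/0.495 = 1.53; P(χ²₃ > 5.12) = 16%.
- m = 27, constant hospital variance 0.05, c = 0.02: e = 0.5 × 0.93 = 0.465; factor 1 + 26 × 0.02/0.485 = 2.07; P(χ²₃ > 3.77) = 29%.
- m = 36, constant hospital variance 0.04, c = 0.01: e = 0.475; factor 1 + 35 × 0.01/0.485 = 1.72; P(χ²₃ > 4.54) = 21% (simulated 21%).
- m = 36, constant hospital variance 0.03, c = 0.02: e = 0.475; factor 1 + 35 × 0.02/0.495 = 2.41; P(χ²₃ > 3.24) = 36% (simulated 35%).

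With five visits and 27 per hospital, simulation gave 18% and 33% for the first two settings.

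**5. Power under a valid analysis.** SE = 0.39 × √(2 × DE/250), with 500 analysed and a t-test on 12 df. At ICC 0.01, SE = 0.0405 and 0.13/SE = 3.21, so power is 0.84. At ICC 0.02, SE = 0.0454 and the ratio is 2.86, so power is 0.75. At ICC 0.05, SE = 0.0577 and the ratio is 2.25, so power is 0.54.

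**The case against.** **The primary test may be protected.** The text speaks of change in the means over time, which is most naturally the group-by-time term, and step 4 shows that constant hospital effects leave that term near 5%. This stands in part. A reader might infer that the primary analysis is bound to have an inflated error rate, and the document does not support that: it gives neither an ICC nor a hospital-by-time variance. But the protection needs every hospital to drift in the same way over 18 months. That is hard to assume when each hospital's own pharmacists and doctors make the medication changes. The t-tests have no such protection.

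**A condensed article leaves model detail to the SAP.** That is true of covariates and degrees-of-freedom methods. Here, however, the article commits to named tests that do not fit its own randomisation, and its sample size rests on the same independence assumption.

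**The strata.** A reader might go further and blame the uneven strata for the inflation, or project unequal patient numbers per arm from them. Neither is supported. Strata of 5 and 3 hospitals cannot be split evenly, and 3:2, 3:3, 1:2 is as close as a 7:7 total allows, apart from its mirror image. Ignoring strata is not the source of the clustering error. The text states 250 per arm, and the site numbers appear to be in Fig. 1, which is not shown. What remains is minor: the intervention arm has one more of the largest hospitals and one fewer of the smallest, which a stratum term handles.

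**Baseline adjustment.** Nor can the t-tests be faulted for leaving out an admission value. Table 1 measures ED visits and readmissions only at 6, 12 and 18 months.

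**Conclusion.** The concern holds as a mismatch between the unit of randomisation and the unit of analysis, and it should be corrected before analysis. For the t-tests, any positive ICC inflates the error rate: 8% to 20% over ICC 0.01 to 0.05 with 27 patients per hospital, and 9% to 24% with about 36. The ANOVA between-group test is affected similarly or more. For the group-by-time test the inflation is conditional: none if hospital effects do not change over time, and roughly 16% to 35% if hospital-by-time variance is 1% to 2% of the total, depending on the number of visits and cluster size. All of these sizes rest on assumed variance components and equal clusters. The direction does not depend on the exact values, provided hospitals differ (t-tests, between-group test) or drift apart over time (group-by-time test).

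**What to change.** Replace the repeated measures ANOVA with a linear mixed model for the post-admission visits:

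- random effects for hospital, hospital-by-visit and patient;
- fixed effects for arm, visit, arm-by-visit and randomisation stratum;
- the admission value of the outcome as a covariate, with admission not also kept as an outcome visit;
- a small-sample degrees-of-freedom correction (Kenward-Roger or Satterthwaite), since there are only 14 clusters.

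Replace the t-tests for ED visits and hospitalisations with a count model that has a hospital random effect and the stratum term. Alternatively, analyse hospital-level means (14 − 2 = 12 df unadjusted, or 14 − 4 = 10 df with the three-level stratum), or use a permutation test within strata.

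**Cost.** No new data; revised wording and modest programming. Confidence intervals will be wider. The stated 90% power no longer holds: with 500 analysed it is about 0.75 at ICC 0.02 and 0.54 at ICC 0.05 on 12 df. The power statement should be restated with an explicit ICC assumption.

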**Discussion:**

This REVMED trial aims to test the hypothesis that a pharmacist-led deprescribing intervention initiated in the hospital will reduce the total number of medications and PIM 18 months after hospital discharge, reducing fall, emergency department visits, readmissions, mortality and lead to improvement in quality of life. Trial findings will quantify the clinical outcomes associated with reducing medications and PIM for hospitalized older adults with polypharmacy.

*Trial registration number:* This trial was prospectively registered at clinicaltrials.gov (NCT05875623) on the 25th of May 2023. NCT05875623 Clinicaltrials.gov URL: NCT05875623 registered on 25th July 2023.

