### Outcome measures

The primary outcome of the trial is the total number of chronic medications and PIM taken by older adults at five time-points (admission, discharge, 6 months, 12 months and 18 months post-randomization).

The secondary outcomes include fall events, number of emergency department visits, number of ADE-related and all-cause readmissions to the hospital, and mortality at 6 months, 12 months, and 18 months post-randomization. The total number of pharmacists' interventions and acceptance by doctors will be measured at discharge. The quality of life will be measured at admission, discharge, 6 months, 12 months, and 18 months post-randomization (Table 1).

**Table 1 Tab1:** Primary and secondary outcomes, instruments, and time-points

	Instruments	Time-points
Primary outcome		
1. PIM	MALPIP	Admission, discharge, 6 months, 12 months and 18 months
2. Chronic medications	Medication prescribed continuously for more than 28 days prior to the assessment day	Admission, discharge, 6 months, 12 months and 18 months
Secondary outcome		
1. Recommendations made by pharmacists and accepted by physicians	Pharmacists’ pharmacotherapy review form and patients’ case note	Discharge
2. Fall event	Medical records and self-reported using ICD-10 codes	discharge, 6 months, 12 months and 18 months
3. Emergency Department (ED) visit	Medical records and self-reported	6 months, 12 months and 18 months
4. ADE-related and all-cause readmissions	Medical records and self-reported	6 months, 12 months and 18 months
5. Quality of life	EQ-5D-5L	Admission, discharge, 6 months, 12 months and 18 months
6. Survival status	National Registration Department database	discharge, 6 months, 12 months and 18 months

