### Sample size calculation

Sample size was calculated based on the primary outcome: the reduction in the mean number of PIM in discharge. According to Wehling et al. [24], the mean number of PIMs at discharge for the intervention group was 0.15, while the mean number of PIMs at discharge for the control group was 0.28 [24]. For an alpha risk of 0.05 and a 90% power, standard deviation 0.39, it was estimated that 189 patients would be needed per arm (378 patients in total) to detect a 0.13 reduction in the mean number of PIM [24]. Projecting a subject dropout rate of 25%, the total number of subjects required will be 500, or 250 per arm. The number of samples per trial site will be stratified based on yearly admissions. Sample size was calculated using Power and Sample size online calculator, compare two proportions, two-sample, two-sided equality test [25].

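### The primary analysis runs over four unnamed time-points, while the primary outcomes are defined at five; the visits, the role of the admission count and the tested contrast need to be reconciled

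*Protocol article*

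**What the plan says.** Protocol article, Outcome measures: the primary outcome is the number of chronic medications and of PIM "at five time-points (admission, discharge, 6 months, 12 months and 18 months post-randomization". Table 1 lists the same five occasions for each of the two outcomes. The Methods paragraph of the abstract also gives five, with enrolment in place of admission.

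Protocol article, Data analysis: the change in the mean of both outcomes "across four time-points will be assessed using repeated measures ANOVA". The four are not named. The sentence does not say whether the admission count is a baseline or one of the repeated levels, and it mentions no comparison of arms. This is the only analysis given for the primary outcomes.

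Two other places point to particular visits. The Sample size calculation section bases the number of patients on "the reduction in the mean number of PIM in discharge". The Discussion paragraph of the abstract states the hypothesis that the intervention "will reduce the total number of medications and PIM 18 months after hospital discharge".

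**The concern.** The one stated primary analysis does not match the definition of the outcomes it analyses. Which visits enter matters because the article relies on two specific ones: discharge for the sample size and 18 months for the hypothesis. If the analysis left out either, it would have no data at a visit the trial is built on.

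The role of the admission count matters too. It is measured before the intervention, so no intervention effect is expected in it. If it is one of the repeated levels, an arm main effect averages that null difference with the later ones. If it is left out of the levels, an arm-by-time test asks only whether the arm difference changes after admission, which is a different question from whether there is a benefit. The answer obtained from the same data can therefore depend on a choice that the text does not fix.

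**Working it through.** **1. The plan's own figure.** Inputs from the Sample size calculation section: "the mean number of PIMs at discharge for the intervention group was 0.15"; "the mean number of PIMs at discharge for the control group was 0.28"; difference 0.28 − 0.15 = 0.13; "For an alpha risk of 0.05 and a 90% power, standard deviation 0.39". For two means, two-sided:

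n per arm = 2 × [0.39 × (1.960 + 1.282) / 0.13]² = 189.1

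This reproduces the stated 189 per arm (378 in total). Dividing by 0.75 for dropout gives 504, close to the stated 500. The sizing is thus a comparison of mean PIM at one visit, discharge.

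**2. What each reading of the four keeps.**

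| Reading | Discharge (sizing) | 18 months (hypothesis) | Admission |
|---|---|---|---|
| Change from admission at the four later visits | kept | kept | baseline |
| Admission dropped | kept | kept | not used |
| Discharge dropped | lost | kept | outcome level |
| 6 or 12 months dropped | kept | kept | outcome level |
| 18 months dropped | kept | lost | outcome level |

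If an effect existed only at the omitted visit, neither the arm term nor the arm-by-time term would have power above the 5% significance level.

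**3. Effect of the role of admission.** Assumptions not in the documents: the effect of 0.13 is the same at every post-admission visit and zero at admission; SD 0.39 at each visit; a common correlation ρ of 0.3, 0.5 or 0.7 between visits; 189 independent patients per arm, so hospital clustering is ignored.

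Arm main effect over k levels:
- mean effect = 0.13 × (post-admission levels) / k
- variance of a patient's mean = 0.39² × [1 + (k − 1)ρ] / k
- noncentrality = (189/2) × (mean effect)² / variance

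Mean effects: four post-admission levels, 0.13; admission plus three, 0.13 × 3/4 = 0.0975 (25% lower); all five, 0.13 × 4/5 = 0.104 (20% lower).

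Example at ρ = 0.5 and k = 4: variance = 0.1521 × 2.5 / 4 = 0.0951. The noncentrality is 94.5 × 0.0169 / 0.0951 = 16.8 without admission and 94.5 × 0.0095 / 0.0951 = 9.45 with it.

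Arm-by-time interaction: noncentrality = (189/2) × Σ(eⱼ − ē)² / [0.39² × (1 − ρ)], where eⱼ is the effect at level j and ē the mean effect; degrees of freedom k − 1 and 376(k − 1).
- Four post-admission levels: every eⱼ equals ē, so it is 0.
- Admission plus three, ρ = 0.5: Σ = 0.0975² + 3 × 0.0325² = 0.012675, and 94.5 × 0.012675 / 0.07605 = 15.75.

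Power at ρ = 0.3 / 0.5 / 0.7:

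| Levels | Arm main effect | Arm by time |
|---|---|---|
| Four post-admission | 99.7% / 98% / 96% | 5% / 5% / 5% |
| Admission plus three later | 94% / 87% / 79% | 81% / 93% / 99.5% |
| All five | 97% / 92% / 84% | 80% / 93% / 99.5% |

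Under each choice of levels at least one term has high power. With four post-admission levels only the main effect does; once admission is a level, the main effect is diluted and the interaction is not.

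**The case against.** The strongest reply is that the sentence speaks of change, and Table 1 has one pre-intervention visit and exactly four later ones. Change from admission at those four fits the wording, keeps both discharge and 18 months, uses admission as baseline and dilutes nothing. This stands as a plausible reading, and nothing in the text favours dropping discharge. But the text does not state it, and under it an arm-by-time test would still miss a constant difference.

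Second, a reader might infer that the missing time-point by itself dilutes the effect or makes a sustained effect undetectable. The documents do not support that. Both consequences depend on which ANOVA term is tested, and none is named. Dilution of the main effect also persists with all five levels (20% against 25%), so changing four to five would not remove it.

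Third, a reader might infer that the hypothesis predicts a constant benefit. It does not: it refers to a reduction at 18 months, and the article's main Discussion section treats sustainability as something the trial will show. Constancy is an assumption of the calculation.

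Fourth, the tested term and the handling of baseline are commonly left to the SAP, which is not shown. That is fair: their absence alone would be no finding, and it cannot be said that the choice is in fact open after the data are seen. What remains is that the article does state a primary analysis, and that statement conflicts with its own outcome definition.

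Last, a baseline covariate is not the only valid use of the admission count; change scores, or admission as a level with the interaction tested, are also defensible. Any of them would do if it were stated.

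**Conclusion.** The conflict between four and five time-points in the primary analysis is certain, and the four cannot be identified from the text. Its consequence ranges from none (change from admission at the four later visits) to loss of the sizing visit or the hypothesis visit. If admission is a repeated level and the arm main effect is tested, a sustained effect shrinks by 25% with four levels or 20% with five. If the four are post-admission and arm by time is tested, a strictly constant effect is detected no more often than the 5% significance level.

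The dilution percentages need only a sustained effect and no difference at admission. The powers also rest on the assumed correlations, equal SDs and independent patients. Because they ignore clustering by hospital, they serve to compare readings and are not achievable powers. The point should be settled before analysis; it is correctable, since data are planned at all five visits.

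**What to change.** Reconcile Data analysis with Outcome measures and Table 1 by stating, for both primary outcomes, that:

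- the outcomes in the model are the counts at discharge, 6, 12 and 18 months;
- the admission count is a baseline covariate and not an outcome level;
- the test is the between-arm difference estimated from this model at one time-point that the sponsor names in advance, and not the omnibus time or arm-by-time term.

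Naming that time-point requires the sponsor to reconcile discharge, used in the Sample size calculation section, with 18 months, used in the abstract's hypothesis. This is a design decision and more than an edit. The cost is a few sentences and that prior choice; the admission count is already collected, so no new data are needed.
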